**Figure 6 F6:**
[figure not shown]
Puncture of V. Subclavia – introducing guiding wire (Seldinger technique).

**Figure 7 F7:**
[figure not shown]
Puncture of V. Subclavia – introducing peel away sheath.

### Primary and secondary endpoints

#### Primary endpoint

The primary endpoint will be the success rate of the randomized implantation technique.

#### Definition of the primary endpoint

Primary success is defined as the correct position of the catheter in the V. Cephalica/V. Subclavia on the intended side controlled intraoperatively by radiography and correct function verified by drawing blood and infusion of fluid.

#### Assessment of the primary endpoint

The primary success will be assessed postoperatively by the responsible physician in the case report file (CRF) and will be confirmed by an independent study nurse and will be compared to the operation report. A copy of the intraoperative radiography showing the right position of the catheter will be saved in the digital radiological picture viewer software Centricity^®- ^used routinely by the University Hospital of Heidelberg.

#### Secondary endpoints

##### Perioperative complications

• pneumothorax

• hematothorax

• intraoperative lesion of nerves

• dislocation of the catheter or the port chamber

• intolerance of contrast agent

##### Postoperative complications

• thrombosis

• postoperative bleeding

• hematoma

• disconnection or breakage of the catheter

• extravasation of injected fluid

• wound infection

• cutaneous necrosis

Definitions are shown in Table 2 and Table 3

**Table 2 T2:** Definitions of perioperative complications.

Pneumothorax	Radiological findings
Hematothorax	Radiological findings or sonografic findings

Intraoperative lesion of nerves	Clinical diagnosis or EMG findings

Dislocation of the catheter or the port chamber	Radiological finding

Intolerance of contrast agent	Any allergic reaction of contrast agent which requires any application of drugs

**Table 3 T3:** Definitions of postoperative complications.

Thrombosis	Sonographic findings or phlebography
Postoperative bleeding	Clinical diagnosis during reoperation

Hematoma	Clinical diagnosis, no reoperation necessary

Disconnection or breakage of the catheter	Radiological findigs, findings after explantation

Extravasation of injected fluid	Radiological findings or clinical diagnosis

Wound infection	Clinical diagnosis. Reopening of wound necessary or antibiotic treatment.

Catheter sepsis	Two or more of the following symptoms:
	• temperature over 38.3°C or under 36°C
	• heart frequency over 90 beats per minute
	• breath frequency over 20 breaths per minut, PaCO2 < 32 mmHg (spontan breathing) or PaO2/FiO2 < 200 mmHg (mechanical ventilation)
	• Total peripheral WBC count > 12 G/L or WBC < 4.0 G/L or > 10% immature neutrophils (bands), regardless of total peripheral WBC count
	• Plasma C-reactive protein > 2 SD above normal value
	**AND**
	Positive findings in bacteriology of the Port catheter pike

Cutaneous necrosis	Clinical diagnosis or histological finding

##### Assessment

1. Perioperative complications of port implantation will be recorded with tick boxes at day of operation by an independent study nurse.

2. Postoperative complications of port implantation will be recorded with tick boxes at day of operation and visit 1 (90 days after operation) after a standardized telephone interview by a study nurse. A confirmation by the responsible family physician will be requested by any abnormality reported by the patient.

The duration of port implantation procedure

• Time from first skin incision to last knot of intracutaneous suture

• Time from patient entering until patient leaving intervention room

##### Assessment

Both times are recorded by an independent study nurse in the CRF at the day of operation.

##### Dose of radiation

Definition: Product of dose rate and surface of radiation (Gy × cm^2^).

##### Assessment

The value will be copied from the display of the used radioscopy device by a study nurse and recorded in the CRF.

### Safety aspects

#### Specification of safety variables

##### Training for surgeons

For surgeons/radiologists and tutors (senior surgeons/radiologists) who operated 25 or fewer ports so far the exact number of operated ports will be noted in the CRF. Surgeons and tutors (senior surgeons) who have performed more than 25 port operations so far will be classified in one of the following categories: 26–30; 31–35; 36–40; 41–45; 46–50; > 50 operated ports and recorded in the CRF.

##### Concomitant medication

Concomitant medication will not be recorded because the primary success rate of the two implantation techniques is a local and technical endpoint. Therefore, a systemic pharmacological interaction with the medication of the patient will be very unlikely.

##### Past medical history

Prior and concomitant illness of the patients will be documented in the CRF. The category of the primary disease (reason for port-catheter implantation) is one of the variables to be analyzed for baseline comparability.

##### Adverse events and serious adverse events

AEs will be reported to the principal investigator in regular intervals during the course of the study. Symptoms anticipated by chemotherapy and progression of malignant illness will not be recorded as AEs as they are not likely related to the surgical implantation technique.

SAEs which meet one of definitions of the secondary endpoints are treated as SAEs regarding their documentation but do not have to be reported to the sponsor (University Hospital of Heidelberg) and principal investigator ([name]. [name], Chairman of the Department of General, Visceral and Transplantation Surgery, University Hospital of Heidelberg) within 24 h. They will be reported to the principal investigator in regular intervals throughout the study. The surgical and radiological trial coordinator will also cross check the SAEs/AEs of all patients.

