### Study organization

All patients scheduled for a primary TIAP system implantation procedure in the Outpatient-Clinic of the Department of Surgery or Radiology, University Hospital of Heidelberg, will be referred to and screened by members of the Clinical Study Center Surgery (KSC). The result of the screening will be recorded in the screening-log.

Approximately 700 patients per year undergo a TIAP system implantation at the Outpatient-Clinic of the Department of Surgery and Radiology at the University of Heidelberg. The estimated time frame to randomize 110 patients will be approximately 6 months.

Sponsor of the PORTAS 2 trial is the University Hospital of Heidelberg.

The independent data management and statistical analysis will be carried out by the Institute of Medical Biometry and Informatics (IMBI) of the University of Heidelberg according to a prespecified Statistical Analysis Plan.

The principal investigator has the right to terminate the trial and to remove all trial material from the trial centre at any time in consultation with the Clinical Study Team Leader and the Biostatistician. Reasons that may require a termination of the trial include the following:

• The incidence or severity of adverse events in this trial indicates a potential health hazard caused by the study treatment

• It appears that patient's enrolment is unsatisfactory with respect to quality or quantity or data recording is severely inaccurate or incomplete

• External evidence that renders the necessity to terminate the trial

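### The adverse-event exclusion for chemotherapy and tumour symptoms makes no exception for signs of a port complication, and catheter sepsis is missing from the listed complications

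*Protocol article*

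**What the plan says.** All places are in the protocol article.

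- **Adverse events and serious adverse events.** The rule is "Symptoms anticipated by chemotherapy and progression of malignant illness will not be recorded as AEs", and the reason given is "as they are not likely related to the surgical implantation technique". The section names no assessor, no criteria for the judgement and no exception. It also says that serious events meeting a secondary-endpoint definition are still documented, and that the surgical and radiological coordinators cross-check the recorded events.
- **Table 3, catheter sepsis.** The clinical part needs "Two or more of the following symptoms". The five signs include "temperature over 38.3°C or under 36°C" and "Total peripheral WBC count > 12 G/L or WBC < 4.0 G/L". The definition also requires, joined by AND, "Positive findings in bacteriology of the Port catheter pike".
- **Table 3, wound infection.** This is a local diagnosis: "Clinical diagnosis. Reopening of wound necessary or antibiotic treatment".
- **Postoperative complications and their Assessment.** Seven complications are listed. A study nurse ticks them off on the day of operation and again at day 90 after a standardized telephone interview. The family physician is asked to confirm abnormalities that the patient reports.
- **Minimizing treatment bias and Minimizing measurement bias.** The antibiotic rule foresees patients whose chemotherapy is due less than 5 days after implantation. Blinding is ruled out.
- **Study organization.** One ground for termination is "The incidence or severity of adverse events in this trial indicates a potential health hazard caused by the study treatment".

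**The concern.** The rule settles cause before anything is written down. An event taken to be an expected effect of chemotherapy or of the tumour leaves no adverse-event record, so nobody can revisit the attribution later. An analysis plan cannot repair this, because the data would not exist.

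This matters most where an anticipated chemotherapy symptom is also an early sign of a port complication. Catheter infection is the obvious case. At stake are how completely port-related harm is ascertained in both arms, and the information available to whoever applies the termination criterion.

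**Working it through.** The plan gives no rate of infection, sepsis or chemotherapy symptoms, so there is no figure to reproduce. The check compares the sections with one another.

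**Step 1. Do the excluded symptoms overlap with the plan's own port signs?** The article does not list the anticipated chemotherapy symptoms. I assume that fever and a low white-cell count are among them.

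| Element of catheter sepsis (Table 3) | Could be taken for a chemotherapy effect? |
|---|---|
| "temperature over 38.3°C or under 36°C" | Yes, as fever |
| "Total peripheral WBC count > 12 G/L or WBC < 4.0 G/L" | Yes, at the low end |
| "Positive findings in bacteriology of the Port catheter pike" | No, specific to the device |

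Two of the five signs meet the clinical part, so fever with a low white count is enough for that part. It is not enough for the diagnosis, which still needs the bacteriology.

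**Step 2. Does the bacteriology criterion close the gap?** Only if a sample is taken. The study visit schedule (Table 1) contains no bacteriology, so a result presumably depends on someone first suspecting the port. A fever put down to chemotherapy may then produce neither a culture nor an adverse-event entry.

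**Step 3. Do the two causes overlap in time?** Yes. The antibiotic rule foresees chemotherapy less than 5 days after implantation, and follow-up runs to day 90.

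**Step 4. Which events have another route into the data?** Table 3 defines eight postoperative complications and the list above it names seven. The difference, 8 − 7 = 1, is catheter sepsis.

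- Thrombosis, bleeding, hematoma, catheter disconnection or breakage, extravasation, wound infection and cutaneous necrosis are listed. They are captured by tick box, and their definitions contain no filter for cause.
- Catheter sepsis is defined but not listed, so it is unclear whether it has a tick box.
- A symptom compatible with a port problem that meets no listed definition has only the adverse-event record.

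**Step 5. Could a later source recover an unrecorded event?** The coordinators' cross-check covers only what was recorded. Under Concomitant medication, medication is not recorded, so later antibiotic use leaves no trace there. The day-90 interview may recover an event, but the physician's confirmation depends on the patient reporting it.

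**Step 6. Scale.** With 50 per group, one unrecorded patient is 1/50 = 2.0 percentage points. With 55 per group (half of the 110 also given as the recruitment target) it is 1/55 = 1.8 points. How many patients would be affected cannot be derived from the document.

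**The case against.** The strongest case on the other side has five parts.

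1. **Most port harms are secondary endpoints with their own capture.** This stands. The adverse-event sentence does not govern the tick boxes. Thrombosis is defined by imaging and wound infection by local findings, so neither can be defined away as a tumour or chemotherapy effect.
2. **Serious events that meet an endpoint definition stay documented.** This stands, and it covers recognised serious sepsis if the Table 3 entry counts as an endpoint definition. It does not help with a fever whose link to the port was never considered, or with non-serious events.
3. **Adverse events are scheduled at the same two contacts as complications.** Correct: Table 1 shows both on the day of operation and at day 90. Changing the rule adds no earlier contact, and sparse follow-up is a separate matter. What changes is whether an event that comes to notice is written down.
4. **The termination criterion is discretionary and has no numeric threshold.** Correct. Nothing stops the principal investigator from also weighing endpoint complications. The criterion is nevertheless worded in terms of adverse events, and those are what the exclusion thins out.
5. **The article condenses a fuller protocol.** Table 1 points to a section 2.6 that does not appear in the article, and exceptions may be set out there. Leaving expected effects of background disease and therapy unlogged, with a reason given, is also a recognised choice. Both points lower the priority. The rule as published is still stated without qualification, and the list and Table 3 still disagree.

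**Conclusion.** The concern holds in a narrow form and is a cheap improvement. As written, the exclusion allows sepsis-like and unlisted port-compatible events to go unrecorded, and so to escape the cross-check and the adverse-event basis for termination. Separately, the list of postoperative complications and Table 3 disagree on catheter sepsis.

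Three stronger readings are tempting, and the document does not support them:

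- A reader might infer that port harms in general are lost to review. They are not: the seven listed complications are recorded independently of the exclusion.
- A reader might infer that fever and a low white count by themselves define port infection. They do not: catheter sepsis also needs positive catheter bacteriology, and wound infection is defined locally.
- A reader might infer a biased comparison between arms, with each department attributing symptoms in its own way. The trial is open, so this is possible. But no section says who makes the attribution, and a study nurse records the postoperative complications. Unequal loss is not shown. Under-recording of harm does not depend on it.

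The conclusion rests on two assumptions: that fever and low white count would be regarded as anticipated chemotherapy symptoms, and that no fuller document carves out an exception. Its size cannot be quantified from the document beyond about 2 percentage points per missed patient in one arm.

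**What to change.** - **Adverse events and serious adverse events.** Limit the exclusion to symptoms that cannot arise from the port or its insertion. Record symptoms compatible with a port complication, for example fever or suspected infection, as adverse events whatever the presumed cause, and enter the suspected cause in a separate CRF field.
- **Reporting.** Tabulate these events by arm twice, once for all events and once after applying the attribution.
- **Postoperative complications.** Add catheter sepsis to the list, so that list and Table 3 agree and it is recorded like the others.

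The cost is one reworded sentence, one CRF field and one list entry with its tick box. The downside is some extra adverse-event entries in about 100 patients, many of them truly due to chemotherapy. No visit, procedure or treatment changes. The change has to be in place before enrolment, because events not recorded at the time may not be recoverable.

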### Analysis

Comparisons will be made of the primary endpoints of both intervention groups for all randomized patients who underwent surgery for TIAP implantation. Patients will be analyzed as randomized. This is in line with the intention-to-treat principle [18]. In addition, a per-protocol analysis will be performed.

The outcome measures of the primary endpoint will be tested for significance with the chi-square test with continuity correction. Fisher's exact test will be used instead if one or more expected cell counts are less than five. No stratification will be used. The estimated odds ratio of primary success will be presented together with a 95% confidence interval. A secondary analysis will be performed using a multiple regression model including treatment group, age, body mass index, surgeon's experience and Karnofsky Index as predictors. All predictors except for treatment group will be used as continuous variables.

Patients with missing information regarding primary success will be considered as failures in all analyses of primary success except for one sensitivity analysis in which these patients will be excluded.

All statistical analyses will be performed using SAS^® ^software, Version 9.1 (or higher) of the SAS System for Unix (SAS Institute Inc., Cary, NC, USA).

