### Number of patients needed

A review of published literature showed a median primary success rate of 80% for the VS in retro- and prospective studies [1,2,9-15]. PVS achieved a median primary success rate of 99% in various retrospective studies [3-8]. The group size for double sided testing was calculated with Simple Interactive Statistical Analysis (SISA) [16]. If the difference in success rate is 19% (80% vs. 99%) there will be an 80% chance that a trial involving 100 patients (50 per group) could detect a significant difference at an alpha level of 5% (Figure 1). We decided to calculate the sample size on the results of previous studies instead of calculating the sample size on a defined minimal clinical important difference because all mentioned previous studies showed a consistent median difference of 19%. This offers the opportunity to test these results the first time in a RCT setting with an economical sample size.

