### Randomization and procedures for minimizing bias

#### Minimizing bias

To achieve comparable groups for known and unknown risk factors randomization will be performed as unstratified block randomization with random block sizes in a 1:1 allocation ratio. Allocation to treatment group will be carried out by the randomization software RITA^®^[17]. 110 patients will be recruited according to the sample size calculation. Randomization will be performed by a study nurse of the Clinical Study Center Surgery (KSC) expertise based to the Department of Surgery for patients in group A and to the Department of Radiology for patients in group B. Randomization will be carried out after patient signed the informed consent. Intervention will be scheduled 1–4 days after inclusion depending on the earliest operation appointment possible.

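### The planned primary test is valid and meets its stated power, but it is conservative; naming Boschloo's exact test would gain about 4 to 5.5 points of power at the design rates within the same 5%

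*Protocol article*

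**What the plan says.** The Analysis section states that the primary endpoint will be "tested for significance with the chi-square test with continuity correction". It adds that Fisher's "exact test will be used instead if one or more expected cell counts are less than five". An odds ratio with a 95% confidence interval accompanies the test, and all analyses are to be run in SAS 9.1 or higher.

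The section on the number of patients needed fixes the operating characteristics. The test is two-sided ("The group size for double sided testing was calculated with Simple Interactive Statistical Analysis (SISA"), and the trial "could detect a significant difference at an alpha level of 5" per cent. The assumed rates are given by "If the difference in success rate is 19% (80% vs. 99" per cent), and the power statement is "there will be an 80% chance that a trial involving 100 patients (50 per group"). The section on minimizing bias gives a larger recruitment figure: "110 patients will be recruited according to the sample size calculation". I therefore show results for both 50 and 55 per arm.

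**The concern.** Primary success is expected to be common: 80% in one arm and 99% in the other. With about 50 patients per arm and few failures, both the continuity-corrected chi-square and Fisher's exact test reject less often under the null than their nominal 5%. The plan combines the two through a switch that depends on the data, which suggests that the choice matters. If both branches are equally conservative, the switch adds nothing and part of the 5% goes unused.

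The 99% figure comes only from retrospective studies, and the protocol says that it took the effect from earlier results, not from a minimal clinically important difference. The true difference may therefore be below 19 points. The unused part of the 5% would then matter more than it does at the design rates.

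**Working it through.** **Inputs from the protocol.** Two-sided alpha 0.05; success 0.80 vs 0.99; stated power 80%; 50 per arm (100 in total) or 55 per arm (110 in total); 1:1 allocation; the test and switch as quoted.

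**1. Reproduce the sample size.** The mean success rate is (0.80 + 0.99)/2 = 0.895.

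- Uncorrected: n = [1.960 × √(2 × 0.895 × 0.105) + 0.842 × √(0.80 × 0.20 + 0.99 × 0.01)]² / 0.19² = (0.850 + 0.347)² / 0.0361 ≈ 39.7, so 40 per arm.
- Continuity-corrected: n′ = (n/4) × [1 + √(1 + 4/(n × 0.19))]² = (39.7/4) × (1 + 1.237)² ≈ 49.6, so 50 per arm.

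The stated 50 per group is the continuity-corrected figure. Sample size and planned test agree.

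**2. Compare the branches of the rule.** I enumerated every pair of failure counts at 50 and at 55 per arm. At each size the switching rule, Fisher alone and the corrected chi-square alone reject exactly the same tables, with no discordant table. At 80% vs 99% and 50 per arm the switch to Fisher occurs with probability 38%, and it never alters significance at 5%.

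**3. Type I error.** This is the sum of the binomial probabilities of all rejected tables when both arms share one success rate. For Boschloo, tables are ordered by the two-sided Fisher p-value, and the rejection threshold is the largest one that keeps the maximum size over the common rate at or below 0.05. At 50 per arm that threshold is a Fisher p of 0.069.

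| Common success rate | Planned, 50/arm | Boschloo, 50/arm | Planned, 55/arm | Boschloo, 55/arm |
|---|---|---|---|---|
| 0.80 | 2.8% | 4.0% | 2.7% | 4.4% |
| 0.85 | 2.4% | 3.6% | 2.5% | 4.4% |
| 0.895 | 1.9% | 3.2% | 2.1% | 4.0% |
| 0.95 | 0.7% | 2.1% | 0.9% | 2.4% |
| Maximum over all rates | 3.5% | 4.9% | 3.2% | 4.7% |

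**4. Power.**

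| Success rates | Planned, 50/arm | Boschloo, 50/arm | Gain (points) | Planned, 55/arm | Boschloo, 55/arm | Gain (points) |
|---|---|---|---|---|---|---|
| 80% vs 99% | 87.1% | 92.6% | 5.5 | 91.3% | 95.3% | 4.0 |
| 80% vs 98% | 77.9% | 84.9% | 7.0 | 83.5% | 89.7% | 6.2 |
| 80% vs 95% | 50.8% | 58.3% | 7.5 | 57.0% | 66.9% | 9.8 |
| 85% vs 99% | 63.7% | 75.9% | 12.2 | 71.0% | 81.5% | 10.4 |

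Gains are taken from unrounded values. At both sizes the planned rejection region lies wholly inside Boschloo's, so no alternative exists at which Boschloo has less power.

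**5. One table by hand.** Take 5 failures in 50 vs 0 in 50. Each expected failure count is 2.5, so the plan uses Fisher: p = 2 × C(50,5)/C(100,5) = 2 × 2,118,760/75,287,520 = 0.056, not significant. Boschloo gives p = 0.035. At 50 per arm, 7 vs 1, 9 vs 2 and 12 vs 4 failures also miss under the plan and are significant under Boschloo.

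**The case against.** The strongest reply is that nothing here is wrong. The planned test is standard, specified in advance and holds its size below 5%. Its conservatism is already paid for, because the sample size carries the same continuity correction (50 against 40 per arm without it). Power at 80% vs 99% is 87.1%, or 91.3% with 55 per arm, against a stated 80%. All of this stands, and it is why the point concerns efficiency only.

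Three stronger readings are tempting and are not supported:

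- **That the plan runs at 2% where the alternative runs at 5%.** Boschloo runs at about 3 to 4% at the expected rates. At a common rate of 0.895 with 50 per arm the contrast is 1.9% vs 3.2%.
- **That about 15 points of power are lost.** A gain of that size arises at 90% vs 99% (27.2% to 41.9%, 50 per arm). The trial was not designed to detect that 9-point difference, and it would probably miss it with either test.
- **That the switch does harm.** It is fixed in advance and changes no decision. Deleting it alone would be cosmetic.

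The shortfall at 80% vs 98% (77.9%, below 80%) also holds only for 50 per arm; with 55 the planned test reaches 83.5%.

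The change is not free. The test is less familiar, may need software other than SAS, and can disagree with the odds-ratio interval in borderline tables or tables with a zero cell. Zero cells are likely under the present plan too: at a 99% success rate, 50 patients have no failure with probability 0.99^50 ≈ 0.61.

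**Conclusion.** The primary test is valid, consistent with the sample size and adequate for its stated power. It uses less of the permitted 5% than it could: about 2% near 90% success and at most 3.5% with 50 per arm. Boschloo's test keeps the maximum at or below 4.9%. It adds 5.5 points of power at the design rates with 50 per arm, 4.0 points with 55, and about 7 to 12 points for somewhat smaller effects with 50 per arm. The improvement is worth making because it needs no further patients or data.

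The figures assume independent binomial outcomes and equal arms of exactly 50 or 55. Slightly unequal arms would shift them, and the exact agreement between the branches was checked only at these two sizes.

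**What to change.** Before any outcome data are seen, change the Analysis section (and the analysis plan to match) as follows:

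- Name the two-sided Boschloo (Fisher-Boschloo) exact unconditional test at 5%, with tables ordered by the two-sided Fisher p-value, as the single primary test.
- Delete the corrected chi-square and the switch on expected counts.
- Report Fisher's exact p-value and the odds ratio with its 95% confidence interval as supporting results. State that significance rests on the primary test if they disagree, and how the interval is obtained when a cell is zero.
- Allow validated software beyond the named SAS release for this test.

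The cost is a few sentences, validation of the software, and a short explanation for readers who do not know the test. Recruitment, visits and data collection are unaffected.

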## Background

The first implantation of a TIAP was performed and described by Niederhuber et al. in 1982. Since then the insertion of a TIAP is a routinely employed technique in patients who need a safe and permanent venous access for chemotherapy, parenteral nutrition, recurrent blood sampling or other reasons [1]. This system needs no external dressing, allows the patient normal physical activity, is probably less prone to infectious complications and will minimize the occlusion rate of the catheter compared to non-totally implantable catheters [1]. TIAPs are being extensively used world-wide and an increase in the number of port placements can be expected. In Germany 70233 TIAP inpatient implantations were performed in 2006 (Federal Statistical Office, Wiesbaden, Germany). The number of TIAP implantations increased constantly at our Department from 169 in 1997 to 754 in 2007.

Today two different approaches to implant a TIAP are usually employed. Venae Sectio (VS) of the cephalic vein performed predominantly by surgeons and Puncture of Vena Subclavia (PVS) performed by interventional radiologists or surgeons. While most common complications can be observed with both techniques such as "pinch off" phenomena, kinking or dislocation of the catheter, subcutaneous hematoma, nerve palsy and wound infection, there are specific risks only associated with PVS like pneumo- and haematothorax [1,2].

Correct placement of the TIAP in the superior Vena Cava is mandatory for optimal and safe function of the central venous access. The median success rate of TIAP implantation via the conventional approach by transsection of the cephalic vein is 80% in various prospective and retrospective trials [2]. In contrast PVS achieved a success rate between 98 to 100%, up to now in retrospective studies [3-8].

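### The odds ratio is the only effect measure named for the primary endpoint; at the planned 99% success rate it has about a 60% chance of being infinite, and no interval is promised for the 19-point difference the trial was sized on

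*Protocol article*

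**What the plan says.** All references are to the protocol article.

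- **Analysis.** The primary endpoint is tested by a continuity-corrected chi-square test, or by Fisher's exact test when an expected count falls below five. The effect measure follows: "The estimated odds ratio of primary success will be presented together with a 95% confidence interval". No other scale is named for the primary endpoint, and the method for the interval is not stated. A secondary multiple regression includes treatment group, without a stated effect measure. Missing primary outcomes count as failures, except in one sensitivity analysis.
- **Number of patients needed.** For VS the planning value is given as follows: "A review of published literature showed a median primary success rate of 80% for the VS in retro- and prospective studies". For PVS the section gives this value: "PVS achieved a median primary success rate of 99% in various retrospective studies". The calculation is two-sided and starts from an absolute difference, worded as "If the difference in success rate is 19% (80% vs. 99". It arrives at 50 patients in each arm, 100 in all, for 80% power with alpha set to 5%.
- **Background.** The range behind the 99% is given: "In contrast PVS achieved a success rate between 98 to 100%, up to now in retrospective studies".
- **Minimizing bias** and **Study organization.** The recruitment figure there is 110, so 55 per arm at 1:1 allocation. Results below are shown for both 50 and 55 per arm.

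**The concern.** When one arm is expected to fail in about 1% of patients and has only 50 or 55 of them, a table with no failure in that arm is a likely result. An odds ratio of success (PVS relative to VS) then divides by zero. The estimate is infinite and no method that uses the observed counts as they stand gives a finite upper limit. If the ratio is inverted, the estimate is 0 with no positive lower limit, which is the same defect.

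The plan provides for sparse tables in the test, through Fisher's exact test, but it reports the effect on the scale that behaves worst in such tables. The trial was sized to check a 19-point difference seen in earlier studies. The reader will want to know how large that difference is and how precisely it has been estimated, and the named effect measure does not say.

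**Working it through.** **Inputs.** VS success 80%, PVS success 99%, two-sided alpha 5%, power 80%, 50 per arm (Number of patients needed). PVS range 98 to 100% (Background). 55 per arm from the 110 patients in Minimizing bias and Study organization. Test rule and odds ratio from Analysis.

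**1. The plan's own figure.** With d = 0.19 and mean rate 0.895:

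n' = [1.960 × √(2 × 0.895 × 0.105) + 0.842 × √(0.80 × 0.20 + 0.99 × 0.01)]² / 0.19² = 39.7

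With continuity correction: n = (n'/4) × [1 + √(1 + 4/(n' × d))]² = 49.6, so 50 per arm. This matches the protocol. The odds ratio implied by the planning rates is (0.99/0.01)/(0.80/0.20) = 24.75.

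**2. Chance of an infinite sample odds ratio.** This needs no PVS failure and at least one VS failure: P = p^n × (1 − 0.80^n), where p is PVS success. The second factor is practically 1, since 0.80^50 is about 0.00001.

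| PVS success | 50 per arm | 55 per arm |
|---|---|---|
| 98% | 36.4% | 32.9% |
| 99% (planning value) | 60.5% | 57.5% |
| 100% | 100% | 100% |

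**3. Among trials that reach significance.** All possible tables were enumerated under the planned test rule, with VS at 80%. At 99% PVS success and 50 per arm, P(significant) = 0.871 and P(significant with no PVS failure) = 0.576, so 0.576/0.871 = 66% of significant trials have the zero cell (61% with 55 per arm). At 98% the share is 44% (38% with 55 per arm).

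**4. Effect of counting missing outcomes as failures.** The protocol gives no missing rate, so these rates are assumptions. If 99% is the technical success rate and a fraction m is missing, P(no PVS failure) = [0.99 × (1 − m)]^50:

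- m = 1%: 36.6%
- m = 2%: 22.0%
- m = 5%: 4.7%

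Table 1 places the assessment of success on the day of operation, so little missing data is to be expected.

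**5. What would be reported.** Two tables close to the planning assumption, with 50 per arm:

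| Successes, PVS vs VS | Odds ratio, exact 95% CI | Difference, 95% score CI |
|---|---|---|
| 50/50 vs 40/50 | infinite; 2.58 to infinity | 20 points; 11.2 to 33.1 |
| 49/50 vs 40/50 | (49 × 10)/(1 × 40) = 12.25; 1.6 to 542 | 18 points; about 7 to 31 |

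For the first table Fisher's exact p is 0.0012. A Newcombe interval for the same difference is 8.7 to 33.0, so finite limits do not depend on the choice of score-type method. Adding 0.5 to every cell makes the odds ratio finite but gives 26.2 with limits 1.5 to 460.

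**The case against.** Several points on the other side stand, and they limit what can be claimed.

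- **The interval method is not fixed here.** A reader might infer that a Wald interval is planned and would be undefined. The article names no method and refers to a prespecified analysis plan that is not shown. Interval method and zero-cell handling are ordinary content of such a plan, so their absence is no finding. What can be criticised is the choice of scale.
- **The result would not be uninterpretable.** A reader might infer that a successful trial would carry no usable effect size. The exact interval still has a lower limit, 2.58 in the first example, and for superiority the lower limit is the informative end.
- **The comparison with 19 points is not impossible.** The primary endpoint is itself a success rate, so the two rates will be reported and can be subtracted. What is not promised is an interval for that difference.
- **The odds ratio may not be the only treatment estimate.** The secondary regression would give another. Its link is not stated; if it is logistic, a zero cell produces a non-finite estimate there too.
- **The 60% rests on one assumed rate.** At 98% success it is 36%, and a zero cell then occurs in fewer than half of significant trials (44% with 50 per arm). Missing outcomes counted as failures lower it further.
- **An odds ratio is a standard measure.** A trial may be sized on two proportions and report one. That argues for keeping it, and it does not argue against adding the difference.

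**Conclusion.** The point holds as a matter of estimation and reporting. At the plan's own 99% and 50 per arm, the named effect measure is more likely than not to be infinite with no finite upper limit: 60.5%, or 57.5% with 55 per arm. With 50 per arm the chance runs from 36% to 100% over the protocol's 98 to 100% range. These figures assume independent patients and no missing outcomes; an assumed 2% missing brings the 60.5% down to 22.0%.

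The documents do not support a stronger reading. The test, its error rate, the power and the superiority conclusion are untouched. The weakness is that the trial is sized on an absolute difference, while the only interval promised for the primary endpoint is on a scale that often has no finite upper end under the planning assumptions. It is a worthwhile improvement to the plan and does not threaten the trial's validity.

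**What to change.** Add one sentence to the Analysis section, or to the statistical analysis plan before the data are analysed: *The difference in primary success rates (PVS minus VS) will be reported with a 95% Miettinen-Nurminen score confidence interval.* Keep the odds ratio beside it and state that its interval will be exact. The odds ratio need not be demoted.

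The cost is one additional reported estimate. Sample size, trial conduct and the significance test do not change.
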